#### Primary Outcome Analysis

For the response rate at 8 weeks, between-group comparisons will be conducted using chi-square tests, with results reported as risk difference and risk ratio with corresponding 95% CIs. To accommodate the repeated-measures structure of the data (assessments at baseline and at weeks 1, 2, 4, 6, and 8), linear mixed-effects models for repeated measures (MMRM) will be used for continuous outcomes, with fixed effects for treatment group, time, and their interaction; baseline scores will be included as covariates; and random intercepts for participants will be specified to accommodate within-subject correlation. Because study 3 cannot blind participants and the IMT arm involves additional engagement, 2 prespecified sensitivity analyses will probe the robustness of the primary treatment effect to expectation and attention effects: (1) the MMRM and the response-rate models will be refitted with baseline CEQ scores added as covariates; and (2) the analyses will be repeated with adjustment for the Bang Blinding Index to explore whether the estimated treatment effect is attenuated after accounting for residual unblinding. Concordance between the primary (unadjusted) and these expectancy-adjusted estimates will be interpreted as evidence regarding the extent to which any observed benefit is attributable to personalization of the stimulus rather than to differential expectancy or attention. Time to response or remission will be compared between groups using Kaplan–Meier survival curves and the log-rank test. For study 3, the primary analysis will follow an intention-to-treat principle, including all randomized participants according to their assigned group. A supplementary per-protocol analysis will include only participants who complete at least 80% of scheduled listening sessions (ie, a minimum of 45 of 56 daily sessions).

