#### Descriptive and Baseline Analyses

Continuous variables with approximately normal distributions will be summarized as mean (SD) and compared between groups using independent-samples 2-tailed *t* tests (with Welch correction when variances are unequal); nonnormally distributed continuous variables will be summarized as median (IQR) and compared using the Mann-Whitney *U* test. Categorical variables will be summarized as counts (%) and compared using chi-square tests (continuity-corrected for 2×2 tables) or the Fisher exact test when expected cell counts are below 5. Baseline demographic and clinical characteristics will be compared across groups to assess the adequacy of randomization in study 3, and baseline CEQ scores will be compared between arms.

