#### Heterogeneity of Target Disorders, Subgroup Analyses, and Multiple Comparisons

Recognizing that MDD, GAD, and PI differ in symptom profiles and neurobiological mechanisms, the primary analysis of study 3 will pool all 3 disorders to maximize statistical power, with diagnostic group included as a stratification factor in the randomization and as a covariate in all pooled models. Treatment × diagnosis interaction terms will be included in the mixed-effects models to assess whether treatment effects vary by disorder. If significant heterogeneity is detected, disorder-specific results will be reported separately. The analytic hierarchy is specified a priori as follows. The pooled treatment effect (IMT vs nonindividualized therapy), adjusted for diagnosis, is the confirmatory primary contrast. Disorder-specific treatment effects (MDD, GAD, and PI analyzed separately) are prespecified secondary, hypothesis-generating analyses. For each disorder, we will report the response-rate difference and the MMRM-derived between-group difference in symptom change with 95% confidence intervals, regardless of statistical significance, so that the direction and precision of the per-disorder estimates are transparent and can inform the design of a future definitive trial. The treatment × diagnosis interaction will be evaluated primarily as a test of effect-modification rather than as a gatekeeper for reporting; disorder-specific estimates will be presented whether or not the interaction term reaches significance, but will be explicitly labeled exploratory. We acknowledge that this pilot is not powered for confirmatory subgroup inference. With approximately 50 participants per arm per disorder (100 per diagnostic group), each disorder-specific contrast has limited power to detect between-arm differences smaller than a large effect, and the trial is powered for precision of estimation rather than for hypothesis testing within subgroups (see Sample Size Calculation). To avoid over-interpreting unstable subgroup estimates, the disorder-specific analyses will be supplemented by a hierarchical Bayesian model in which disorder-specific treatment effects are treated as exchangeable and shrunk toward the overall pooled effect; this borrows strength across the 3 disorders and yields more stable, less extreme per-disorder estimates than fully separate analyses. Posterior means and 95% credible intervals for each disorder will be reported alongside the frequentist estimates. We will not draw definitive efficacy conclusions for any individual disorder from study 3; rather, the per-disorder estimates will be used to generate hypotheses and to inform stratified sample-size planning for the definitive trial. It should be noted that the music therapy protocol uses the same affective trajectory for participants with MDD and GAD, whereas a distinct biphasic trajectory is used for participants with PI. This difference in trajectory design reflects the distinct clinical objectives for each disorder and will be accounted for in the analysis by including trajectory type as a covariate in sensitivity analyses. Because trajectory type is collinear with the PI-versus-(MDD and GAD) distinction, this covariate adjustment will be reported as a sensitivity analysis complementary to the disorder-stratified analyses above. For the family of disorder-specific secondary contrasts, the false discovery rate will be controlled using the Benjamini–Hochberg procedure, and both adjusted and unadjusted *P* values will be reported.

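### Study 3's primary response-rate test is a plain chi-square, but the confirmatory contrast is defined as adjusted for diagnosis: the two sections name different primary analyses

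*Protocol article*

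**What the plan says.** Three statements in the Protocol article bear on the pooled response-rate comparison in study 3.

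- **Primary Outcome Analysis** names the method: "For the response rate at 8 weeks, between-group comparisons will be conducted using chi-square tests", reported as a risk difference and risk ratio with 95% CIs. No stratification or covariate is mentioned. The same section later requires that "the MMRM and the response-rate models will be refitted with baseline CEQ scores added as covariates", and speaks of "Concordance between the primary (unadjusted) and these expectancy-adjusted estimates".
- **Heterogeneity of Target Disorders, Subgroup Analyses, and Multiple Comparisons** pools the three disorders "with diagnostic group included as a stratification factor in the randomization and as a covariate in all pooled models". It then fixes the hierarchy: "The pooled treatment effect (IMT vs nonindividualized therapy), adjusted for diagnosis, is the confirmatory primary contrast".
- **Descriptive and Baseline Analyses** says categorical variables will be "compared using chi-square tests (continuity-corrected for 2×2 tables) or the Fisher exact test when expected cell counts are below 5". The primary-outcome section does not repeat or exclude the continuity correction.

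The Sample Size Calculation section gives one control response rate (70%), 50 participants per arm in each diagnostic group and a 20-point threshold for clinical importance. It bases the size on precision, not power.

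**The concern.** The test named for the primary endpoint does not estimate or test the contrast that the plan calls confirmatory. A 2×2 chi-square compares the two arms' overall response proportions and ignores diagnosis. The only other method in the primary-outcome section is the mixed model, which is for continuous outcomes. The response-rate models that are to be refitted with expectancy scores have no defined base model.

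Two things are at stake. First, an analyst could report the primary result with or without diagnosis and cite the protocol for either, which is the choice that a prespecified hierarchy should remove. Second, when randomization is stratified on a factor that predicts outcome, an analysis that ignores the factor uses a variance containing between-stratum variation that the design has already balanced out. The test is then conservative and the interval too wide. Response is defined on a different scale for each disorder (MADRS, HAMA or PSQI), so differing rates are plausible, although the protocol does not state them.

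**Working it through.** **Inputs from the protocol.** 3 diagnoses, 50 per arm in each, so N = 150 per arm pooled; 1:1 allocation; two-sided α = 0.05; control rate 70%; threshold of 20 points. **Assumed:** the spread of control rates across diagnoses, always averaging 70%.

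**1. The plan's own figure.** The stated half-width is about 8 to 12 points for 50 per arm, control 70% and differences of 0 to 30 points. Using z·√[p₁(1−p₁)/50 + p₂(1−p₂)/50]:

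- z = 1.282 gives 11.75 (difference 0) down to 8.31 (difference 30), which reproduces the range.
- z = 0.842, the literal one-sided 80% value, gives 7.71 to 5.45, which does not. That labelling matter is separate, and nothing below depends on it.

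**2. Why the pooled test is conservative when rates differ.** With equal arms in every stratum, the pooled risk difference equals the equally weighted stratified one, so only the variance differs. Under no treatment effect:

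- variance assumed by the pooled chi-square: (2/N)·p̄(1−p̄), with p̄ = 0.70, so p̄(1−p̄) = 0.21
- true variance under stratified allocation: (2/N)·mean of pₖ(1−pₖ)

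The true size is about 2[1 − Φ(1.96/√ratio)], where ratio = true/assumed.

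- 70/70/70: ratio 1; size 5.0%.
- 80/70/60: (0.16 + 0.21 + 0.24)/3 = 0.2033; ratio 0.968; 1.96/0.984 = 1.992; size 4.6%.
- 85/70/55: (0.1275 + 0.21 + 0.2475)/3 = 0.195; ratio 0.929; 1.96/0.964 = 2.034; size 4.2%.
- 90/70/50: (0.09 + 0.21 + 0.25)/3 = 0.1833; ratio 0.873; 1.96/0.934 = 2.098; size 3.6%.

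**3. Simulation** (400,000 trials per scenario). The pooled statistic is d²/[p̄(1−p̄)·2/N]. The CMH statistic is [Σ(yₖ − mₖ/2)]²/ΣVₖ, where yₖ is the number of IMT responders and mₖ all responders in stratum k, n = 50, and Vₖ = n²mₖ(2n−mₖ)/[(2n)²(2n−1)]. Each cell shows uncorrected chi-square / continuity-corrected chi-square / CMH, in %.

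| Control rates | Type I error | Power at +10 | Power at +20 |
|---|---|---|---|
| 70/70/70 | 5.0 / 3.7 / 5.0 | 52.0 / 46.5 / 51.8 | 99.4 / 99.1 / 99.4 |
| 80/70/60 | 4.7 / 3.4 / 5.0 | 52.0 / 46.4 / 53.3 | 99.5 / 99.2 / 99.6 |
| 85/70/55 | 4.3 / 3.1 / 5.0 | 51.9 / 46.2 / 55.1 | 99.5 / 99.3 / 99.6 |
| 90/70/50 | 3.6 / 2.6 / 5.0 | 52.1 / 46.1 / 58.3 | 99.6 / 99.4 / 99.7 |

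Power at +10 uses a constant risk difference. In the last row this takes one stratum to 100%; with a common odds ratio giving the same average benefit, CMH power there is 56.6% against 52.1% uncorrected. The +20 figures in the last two rows use a common odds ratio, because a constant difference would exceed 100%.

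**4. Interval width.** The mean 95% half-width for the risk difference under no effect, unstratified against stratified, is 10.33 against 10.10 points at 80/70/60 and 10.34 against 9.59 at 90/70/50.

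**5. Continuity correction, if it applies.** The uncorrected-to-corrected drop at +10 is 52.0 − 46.5 = 5.5 points with equal rates and 52.1 − 46.1 = 6.0 at the widest spread. This loss has nothing to do with stratification.

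**The case against.** The case against giving this much weight is substantial, and most of it stands.

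- *The loss is conditional.* A reader might infer that the chi-square is conservative and wastes power as such. The protocol does not support that. It plans on 70% throughout, and with equal rates the uncorrected chi-square and CMH perform alike.
- *Larger losses need inputs that the protocol does not give.* Control rates of 85/70/40 or 80/60/25 would put power for a benefit of about 10 to 12 points at 59% against 66%, or 53% against 62%. Those rates average 65% and 55%, not 70%.
- *The continuity correction is not stated for the primary test.* It appears only under descriptive and baseline analyses. The wording there is general and could be carried over, but that is an inference.
- *The label unadjusted is weak evidence.* In context it is set against the expectancy-adjusted estimates and most naturally means not adjusted for expectancy. It does not show that adjustment for diagnosis was rejected.
- *No stated figure is invalidated.* The trial is a pilot sized on precision, and type I error was not inflated in any scenario computed.
- *Adjustment was evidently intended, and a later analysis plan could supply the estimator.* The first part is fair. But the article does not merely leave the estimator open. It names a specific test, and that test cannot produce the contrast it calls confirmatory. This part of the objection does not remove the conflict.

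**Conclusion.** The contradiction is in the text and needs no assumption: one section makes a plain chi-square the primary response-rate analysis, another makes the diagnosis-adjusted pooled effect the confirmatory contrast, and the sensitivity analysis refits a model that is never defined.

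The numerical consequence is modest, in the conservative direction, and rests on response rates differing by diagnosis. With control rates averaging 70% and spread by ±10 to ±20 points, type I error is 4.7% to 3.6% instead of 5.0%, and power at a 10-point benefit is about 52% instead of 53% to 58%. With equal rates there is no loss. At the protocol's 20-point threshold, power is about 99% or more for every test and the loss is under 0.5 point. If the continuity correction were also applied to the primary test, size would be 3.7% even with equal rates, and power at 10 points would fall by a further 5 to 6 points.

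The reason to act is the ambiguity over the confirmatory analysis; the power loss alone would not be decisive.

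**What to change.** Reconcile the two sections by naming one primary response-rate analysis for study 3 that uses diagnosis. Either of these would satisfy the stated contrast:

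- a CMH test stratified by diagnosis, without continuity correction, with a stratified risk difference and risk ratio and their 95% CIs; or
- logistic regression on arm and diagnosis, with a standardized risk difference and 95% CI.

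In either case, write down the logistic model as the response-rate model that is refitted with CEQ scores. State that the continuity correction in the descriptive section does not apply to the primary test, and keep the plain chi-square as supportive only.

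The cost is protocol and analysis-plan wording, with no extra data, participants or visits. It should be settled before any outcome comparison by arm is seen.

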### Randomization and Blinding

For the RCT, an independent biostatistician will generate the allocation sequence using SAS software (version 9.4; SAS Institute). Randomization will be managed via a secure, web-based system to ensure allocation concealment. Upon confirmation of eligibility and completion of baseline assessments, the system will release the assignment to a research nurse who is not involved in outcome assessment. Outcome assessors will remain blinded to group assignment throughout the trial. Given the nature of the intervention, complete participant blinding is not feasible, as those in the IMT arm engage in weekly preference assessments and music selection, whereas participants in the nonindividualized arm receive therapist-curated tracks without weekly customization. Beyond the impossibility of participant blinding, we explicitly recognize that the weekly preference assessment and track-rating procedure in the IMT arm constitutes an additional, potentially active, component of participant–researcher interaction and engagement that is not present in a conventional nonindividualized protocol. Any between-arm difference in outcomes could therefore reflect not only the personalization of the musical stimulus itself but also this greater attention, engagement, and sense of agency. To mitigate both expectation bias and this attention and engagement confound, several strategies are used: (1) participants in both arms are informed only that they will receive music therapy, without being told which approach is hypothesized to be superior; (2) all participants complete equivalent contact time and daily listening schedules; specifically, participants in the nonindividualized arm complete a weekly music-experience questionnaire covering their listening experience, mood, and engagement, that is matched to the IMT arm’s weekly preference assessment in length, frequency, mode of administration, and degree of staff contact, so that the 2 arms are equated for attention and procedural engagement and differ only in whether the questionnaire responses are used to regenerate the following week’s music; and (3) primary outcomes are assessed by independent raters who have no knowledge of treatment allocation. In addition, to render expectation effects measurable rather than merely assumed, all participants complete a validated treatment-credibility and outcome-expectancy measure (the Credibility/Expectancy Questionnaire, CEQ) after allocation and before the first session; baseline expectancy scores will be compared between arms and entered as a covariate in prespecified sensitivity analyses of the primary outcomes. To assess the integrity of assessor blinding and to characterize residual participant unblinding, both participants and outcome assessors will be asked to guess the participant’s allocation at week 8, and a blinding index (bang blinding index) will be computed and reported. Unblinding of assessors is permitted only in the event of a medical emergency.

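### Adjusting for the Bang Blinding Index is aliased with treatment, and neither sensitivity analysis can separate personalization from attention as the reading rule claims

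*Protocol article*

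**What the plan says.** Under Primary Outcome Analysis, the article names two prespecified sensitivity analyses for Study 3. The first refits the MMRM and the response-rate models with CEQ scores, described as baseline scores, as covariates. In the second, "the analyses will be repeated with adjustment for the Bang Blinding Index to explore whether the estimated treatment effect is attenuated". Agreement between the unadjusted and the adjusted estimates "will be interpreted as evidence regarding the extent to which any observed benefit is attributable to personalization of the stimulus", as opposed to differential expectancy or attention.

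Under Randomization and Blinding, "both participants and outcome assessors will be asked to guess" the allocation at week 8, and "a blinding index (bang blinding index) will be computed and reported". No participant-level form of the index is given there or elsewhere. The same section has the CEQ completed "after allocation and before the first session", and Study Procedure and Data Collection repeats that timing.

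The models that would take these covariates already carry treatment. The MMRM is specified "with fixed effects for treatment group, time, and their interaction", plus baseline score. The section on heterogeneity of disorders adds diagnosis as a covariate in all pooled models and states: "Treatment × diagnosis interaction terms will be included in the mixed-effects models".

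**The concern.** The article recognises that unblinded participants and greater engagement in the IMT arm could explain a benefit of IMT. These two analyses are its stated statistical adjustment for that threat, and the reading rule says what their results will mean. If one analysis returns the unadjusted estimate by construction, and the other adjusts for a variable that does not carry attention, then agreement says little about personalization. The risk is a published claim that the music itself explains the benefit, resting on an agreement that would also appear if attention explained all of it.

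**Working it through.** There is no stated figure to reproduce. The check is whether the models can be estimated and what agreement would mean.

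**1. Is the index estimable beside treatment?**

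The Sample Size Calculation gives 50 participants per arm in each of three diagnostic groups, hence 150 per arm and 300 in all. Within an arm, the Bang index is the number of correct guesses minus the number of incorrect guesses, divided by the number in the arm. Each participant in an arm therefore has the same value:

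index = B0 + (B1 − B0) × arm.

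This is a combination of the intercept and the arm column, whatever B0 and B1 are. With assumed values 0.1 and 0.6 (and equally with −0.2 and 0.8, or 0.3 and 0.3 in the pooled model):

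| Model | Columns | Rank |
|---|---|---|
| Pooled: intercept, arm, 2 diagnosis terms, index by arm | 5 | 4 |
| MMRM: intercept, arm, 4 time, 4 arm × time, baseline score, index by arm | 12 | 11 |
| Index by arm and diagnosis, main effects only | 5 | 5 |
| Index by arm and diagnosis, with 2 arm × diagnosis terms | 7 | 6 |

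Using assessor guesses gives a second index, which is also constant within arm. Computing the index separately by diagnosis helps only while arm × diagnosis is left out. There are then six cells and four main-effect parameters, so the index coefficient is estimated from the two interaction degrees of freedom (6 − 4 = 2). In other words, it reads treatment-by-diagnosis heterogeneity as if it were unblinding. In the mixed models, where the article includes that interaction, the index is aliased again.

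**2. What does agreement after CEQ adjustment show?**

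Take an illustrative linear model in SD units (all effects assumed):

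CEQ = a × arm + c × U + noise (variance 1 within arm)

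Outcome = (personalization + attention) × arm + b × CEQ + d × U + noise

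U is an unmeasured common cause with variance 1. Then:

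- unadjusted effect = personalization + attention + a × b
- CEQ-adjusted effect = personalization + attention − a × c × d

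| Scenario | Unadjusted | Adjusted |
|---|---|---|
| Personalization 0.40, a = 0 | 0.40 | 0.40 |
| Attention 0.40, personalization 0, a = 0 | 0.40 | 0.40 |
| Expectancy only: a = 0.5, b = 0.4, no U | 0.5 × 0.4 = 0.20 | 0.00 |
| Personalization 0.30, a = 0.5, b = 0, c = d = 0.6 | 0.30 | 0.30 − 0.5 × 0.36 = 0.12 |
| Personalization 0, a = 0.5, b = 0.4, c = 0.6, d = −0.6 | 0.20 | 0 + 0.5 × 0.36 = 0.18 |

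The first two rows give the same agreement from opposite causes. The third shows the analysis working as intended when there is no shared cause. The last two show false attenuation and false agreement when there is one. Randomization does not rule out a shared cause of CEQ and outcome.

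**3. Would each participant's own week-8 guess serve instead?**

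The article does not propose this, but it is an obvious repair. Assume response of 70% (the article's control rate) versus 80%, a true difference of 10 points. Assume also logit P(guess IMT) = −1.5 + bA × arm + bY × response. Fitting a logistic model of response on arm and guess to the exact cell probabilities, and standardising, gives:

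| Coding of the guess | bA | bY | Adjusted difference (points) |
|---|---|---|---|
| Guessed IMT | 1 to 2 | 0 | 10.0 |
| Guessed IMT | 1 to 2 | 0.25 to 0.5 | 9.0 to 5.7 |
| Guessed IMT | 1 to 2 | 1 to 1.5 | 5.6 to −2.1 |
| Guess correct | 1 to 2 | 0.25 to 1.5 | 10.0 to 11.5 |

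The model can be fitted. Because the guess is taken at the outcome visit, it can be biased, but the size and even the presence of bias depend on coding and on coefficients that the article does not supply.

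**The case against.** Several points on the other side have weight.

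- **The operational form could be left to the SAP**, which is to be finalised before database lock. That would cover an unspecified detail. Here the article names the covariate and says how the result will be read, and no arm-level form of the index makes that work.
- **The index by arm and diagnosis has full rank with main effects only**, and the interaction is placed in the mixed models, not explicitly in the response-rate model. This stands as far as it goes. For the binary outcome the analysis is then possible, but uninformative about unblinding.
- **The CEQ timing is openly stated and sensible.** This stands. Expectancy created by learning one's allocation can only be measured afterwards, and the score precedes any music. A reader might infer that the timing is an error and that a CEQ before allocation is needed. The documents do not support that: such a score could not detect a difference in expectancy created by allocation. Only the baseline label and the interpretation need correcting.
- **Attention is handled by design and the rule is hedged.** The control questionnaire is matched in length, frequency, mode and staff contact, and the rule speaks only of evidence regarding an extent. Strengths and Limitations concedes residual confounding and says that clean separation needs a 3-arm design; Future Directions repeats the 3-arm proposal. These concessions lower the severity. They do not rescue the rule, because they say that this trial cannot deliver the separation the rule claims to inform.
- **A reader might infer that the plan would make a real benefit look like an unblinding artefact.** The documents do not support this. It needs the individual guess as covariate, coded as guessed IMT, with response strongly driving the guess. The article plans none of these, and coding the guess as correct leaves almost no bias in the same example.

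**Conclusion.** The point holds, at moderate severity. Sensitivity analysis (2) is aliased with treatment (rank 4 of 5 pooled, 11 of 12 in the MMRM, 6 of 7 with the index by diagnosis and the planned interaction). It therefore either fails or reproduces the unadjusted estimate. This rests only on the index being a group summary, not on any assumed value.

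The CEQ analysis can be fitted, but it is a mediator-type analysis that needs the assumption of no unmeasured common cause of CEQ and outcome. A score taken before the first session also cannot reflect engagement that builds over 8 weeks. Neither covariate measures attention, so the reading rule is unsupported on that part and conflicts with the article's own statement about a 3-arm design. The SD-unit effects and the guess-model figures are illustrations under assumptions, not predictions for this trial.

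It would go too far to infer that the trial's main result is compromised. The intention-to-treat comparison, its confidence interval and the sample size do not depend on these analyses. What changes is the explanation the authors may attach to a difference.

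**What to change.** - Delete sensitivity analysis (2). Report the Bang index descriptively by arm, separately for participants and assessors.
- Describe the CEQ as a post-allocation, pre-treatment measure instead of a baseline one. Report it by arm, and label the CEQ-adjusted model exploratory and mediator-type, stating the assumption of no unmeasured common cause of CEQ and outcome.
- Remove attention from the concordance sentence, limit that sentence to initial expectancy, and cross-refer to Strengths and Limitations.

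No pre-allocation CEQ is needed. The cost is wording in the article and the SAP before database lock. No data collection, sample size or primary analysis changes.

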### Sample Size Calculation

Study 3 is a pilot RCT designed to assess feasibility and to generate preliminary effect estimates to inform a definitive future trial. Accordingly, the sample size is based on precision estimation rather than formal power calculation. The primary outcome is the response rate at 8 weeks, defined as a reduction of 50% or greater from baseline in the disorder-specific symptom severity score. We adopted a minimal clinically important difference–anchored CI approach, setting a 20-percentage-point absolute difference in response rates as the threshold for clinical importance. With 50 participants per arm within each diagnostic group, the expected 1-sided 80% CI half-width for the between-group difference in response rates is approximately 8 to 12 percentage points (derived from a response rate of 70% for the control group and a range of between-group differences from 0% to 30%), thereby permitting precise estimation of feasibility metrics and preliminary efficacy signals to plan the definitive trial.

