### Outcome Measures

#### Primary Outcome Measure

Response rate at 8 weeks, defined as ≥50% reduction in MADRS, HAMA, or PSQI scores; change in quantitative EEG characteristics from baseline to week 8. Specific EEG features of interest are detailed in the statistical analysis plan.

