#### Secondary Outcome Measure

The secondary outcome is change in MADRS, HAMA, and PSQI scores.

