### Plan for Statistical Analysis

All statistical analyses will be performed using SPSS Statistics (version 23; IBM Corp), R (version 4.3 or higher; R Foundation for Statistical Computing), and MATLAB (MathWorks) with the EEGLAB toolbox for EEG data processing. All hypothesis tests will be 2-sided, with a significance level of *α*=.05.

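### Study 3's confirmatory contrast names no endpoint or model, and the one stated test of the primary outcome cannot give the diagnosis-adjusted effect it requires

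*Protocol article*

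**What the plan says.** All references are to the protocol article.

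- Sample Size Calculation, on study 3: "The primary outcome is the response rate at 8 weeks, defined as a reduction of 50% or greater from baseline".
- The section on the primary outcome measure lists two items: "Response rate at 8 weeks, defined as ≥50% reduction in MADRS, HAMA, or PSQI scores; change in quantitative EEG characteristics from baseline to week 8".
- Secondary Outcome Measure: "The secondary outcome is change in MADRS, HAMA, and PSQI scores".
- Plan for Statistical Analysis: "All hypothesis tests will be 2-sided, with a significance level of" .05.
- Primary Outcome Analysis: a chi-square test for week-8 response, an MMRM for continuous outcomes, and then "Time to response or remission will be compared between groups using Kaplan–Meier survival curves and the log-rank test". Two sensitivity analyses are said to test the robustness of the primary treatment effect. In the first, "the MMRM and the response-rate models will be refitted with baseline CEQ scores added as covariates".
- Heterogeneity of Target Disorders, Subgroup Analyses, and Multiple Comparisons: "The pooled treatment effect (IMT vs nonindividualized therapy), adjusted for diagnosis, is the confirmatory primary contrast". The same section makes diagnosis a stratification factor in the randomisation and a covariate in every pooled model, and puts the treatment-by-diagnosis terms in the mixed-effects models. Its multiplicity rule is "For the family of disorder-specific secondary contrasts, the false discovery rate will be controlled using the Benjamini–Hochberg procedure".

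**The concern.** The outcome sections and the analysis sections do not identify the same thing as the bearer of the confirmatory claim. The outcome sections point to week-8 response. The hierarchy asks for a pooled, diagnosis-adjusted effect without saying of what, and the only fully described model that could supply one is the MMRM, whose outcome is secondary. The robustness checks on the primary effect are also run on the MMRM.

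What is at stake is the headline result. When the trial reports, an author could present response, the MMRM contrast or a log-rank result as the confirmatory finding and cite some part of the text for it. The article calls the contrast confirmatory, hypothesises superior response rates, and links a definitive trial to promising pilot results, so the choice of headline matters even in a pilot.

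**Working it through.** **1. The plan's own figures.** The article gives .05 per test and no overall error rate for the primary analysis. Its one figure for the primary outcome is a half-width of about 8 to 12 points with 50 per arm and 70% control response. The formula is z × √[p1(1−p1)/n + p2(1−p2)/n].
- p2 = 0.70: 1.282 × √(0.21/50 + 0.21/50) = 11.75 points.
- p2 = 1.00: 1.282 × √(0.21/50 + 0) = 8.31 points.

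This reproduces 8 to 12 with z = 1.282, a two-sided 80% interval. The stated one-sided 80% (z = 0.842) would give 7.71 to 5.45. That label does not affect the present point. What matters is that the trial was sized on response, which supports response as the primary clinical outcome.

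**2. The sections side by side (clinical outcomes).**
- Week-8 response: primary in the outcome sections; tested by chi-square; diagnosis adjustment not specified.
- Score change: secondary in the outcome sections; analysed by MMRM under the primary heading; included in the sensitivity analyses of the primary effect.
- Time to response or remission: in no outcome list; log-rank under the primary heading.
- Confirmatory contrast: pooled and diagnosis-adjusted; no endpoint, no model.

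**3. Can the stated test deliver the stated contrast?** A chi-square test on the arm-by-response table takes no covariate, so it cannot be adjusted for diagnosis. Nor can it be refitted with expectancy scores. The response-rate models mentioned for that refit imply a regression that the section never describes.

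The gap is one of specification and not of bias. With 50 per arm in each of three strata, the Mantel-Haenszel weight is 50 × 50/100 = 25 in every stratum, so the stratified risk difference equals the crude one. Only the standard error and the test change.

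**4. Error rate if one endpoint governs.** With week-8 response as the only confirmatory test, it is 5%.

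**5. Error rate if any of several tests could count.**
- Three independent tests: 1 − 0.95³ = 14.3%, as a benchmark.
- Three equally correlated normal test statistics (1,000,000 draws): 12.6% at correlation 0.5, 10.9% at 0.7, 9.8% at 0.8, 8.4% at 0.9.
- Simulated null trials: 3 × 50 = 150 per arm; visits at weeks 1, 2, 4, 6 and 8; week-8 response 50% or 70% in both arms; three levels of within-person noise; 5,000 trials in each of six scenarios. The tests were chi-square on week-8 response (no continuity correction), a baseline-adjusted week-8 score contrast standing in for the MMRM, and log-rank on time to first response.
  - Response or score: 7.7% to 8.7%.
  - Response, score or log-rank: 9.2% to 12.1%, or 1.8 to 2.4 times 5%.
  - With a separate remission log-rank (assumed cut-off, score of 7 or less): 11.5% to 15.8%.

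The Monte Carlo standard error is about 0.4 to 0.5 points.

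**6. Coverage by multiplicity rules.** Benjamini-Hochberg covers the disorder-specific contrasts and, in the EEG section, feature families. Neither reaches the pooled response, MMRM and log-rank tests.

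**The case against.** A reader might infer that the plan lets a positive primary be declared on any of three tests at about twice the stated alpha. The documents do not support that. Week-8 response is named as a primary outcome in the abstract, the sample-size section and the outcome section, and the discussion states the hypothesis in terms of response rates. Score change is expressly secondary. Time to response or remission is not listed as an outcome, so it has no claim to primary status. No sentence says that a significant MMRM or log-rank result counts as primary success.

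The heading is also weak evidence. There is no separate heading for secondary clinical analyses, and the same section holds the per-protocol and sensitivity analyses, which nobody would read as primary. Study 3 is a pilot sized for precision, and a prespecified SAP is promised before database lock. The order of testing among secondary outcomes is ordinary SAP content, and its absence here is no finding.

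All of this stands, and it removes any claim that the plan itself runs at an inflated error rate. It does not remove the mismatch in the text: the hierarchy sentence names no endpoint, the stated response test cannot give the adjusted contrast, and the robustness checks treat a secondary analysis as carrying the primary effect. These are things the article states, and an SAP that is not shown does not cure them.

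**Conclusion.** The point holds as an internal inconsistency. The Primary Outcome Analysis and Heterogeneity sections need to be brought into line with the sample-size and outcome sections.

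If the outcome definitions govern, the error rate of the primary claim is 5%. The figure of about 9% to 12% applies only if the ambiguity were used to claim success on any of response, MMRM or log-rank. It rests on assumptions that the article does not supply: visit trajectories, within-person noise and hence correlations, complete data, and a single symptom scale where the trial uses three.

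The pilot status limits the consequence, but the article's own word confirmatory makes it worth settling which result that word belongs to. The inconsistent status of the EEG outcomes is a separate matter and is not part of this point.

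**What to change.** 1. In the Heterogeneity section, state that the single confirmatory clinical contrast is the pooled week-8 response-rate difference between IMT and nonindividualized therapy.
2. In the Primary Outcome Analysis section, replace the unadjusted chi-square as the primary test with a diagnosis-stratified or diagnosis-adjusted estimate of that difference, for example a Mantel-Haenszel risk difference, or logistic regression with a standardised risk difference. The expectancy sensitivity analysis can then refit the named regression.
3. Label the MMRM as the analysis of the secondary outcome.
4. Label the log-rank analyses of time to response or remission as exploratory.

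If the investigators instead want all three tests as routes to success, each would need a level such as 0.05/3 = 0.0167 to hold the overall rate at or below 5%.

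The cost is wording in the article and the SAP, with no change to sample size, visits or data collection. The downside is that a significant MMRM or log-rank result can no longer be presented as the primary result.
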